# Protocol for a prospective, controlled, cross-sectional, diagnostic accuracy study to evaluate the specificity and sensitivity of ambulatory monitoring systems in the prompt detection of hypoxia and during movement

**DOI:** 10.1136/bmjopen-2019-034404

**Published:** 2020-01-12

**Keywords:** hypoxia, ambulatory monitoring, vital signs, wearable devices

## Abstract

**Introduction:**

Automated continuous ambulatory monitoring may provide an alternative to intermittent manual vital signs monitoring. This has the potential to improve frequency of measurements, timely escalation of care and patient safety. However, a major barrier to the implementation of these wearable devices in the ward environment is their uncertain reliability, efficiency and data fidelity. The purpose of this study is to test performance of selected devices in a simulated clinical setting including during movement and low levels of peripheral oxygen saturation.

**Methods and analysis:**

This is a single centre, prospective, controlled, cross-sectional, diagnostic accuracy study to determine the specificity and sensitivity of currently available ambulatory vital signs monitoring equipment in the detection of hypoxia and the effect of movement on data acquisition. We will recruit up to 45 healthy volunteers who will attend a single study visit; starting with a movement phase and followed by the hypoxia exposure phase where we will gradually decrease saturation levels down to 80%. We will simultaneously test one chest patch, one wrist worn only and three wrist worn with finger probe devices against ‘clinical standard ‘and ‘gold standard’ references. We will measure peripheral oxygen saturations, pulse rate, heart rate and respiratory rate continuously and arterial blood gases intermittently throughout the study.

**Ethics and dissemination:**

This study has received ethical approval by the East of Scotland Research Ethics Service REC 2 (19/ES/0008). The results will be broadly distributed through conference presentations and peer-reviewed publications.

**Trial registration number:**

ISRCTN61535692 registered on 10/06/2019.

Strengths and limitations of this studyControlled hypoxia exposure in a standardised environment for all participants.Outcome comparison with both clinical and gold standards.Largest study in healthy volunteers.Once specificity and sensitivity have been established in healthy volunteers; devices will be tested in the target hospital population.

## Introduction

Failure to recognise and act on physiological indicators of worsening acute illness in hospital wards is a prevalent problem recognised over twenty years ago.^1^ Current practice involves the use of early warning scoring systems which monitor standard vital signs. These include intermittent measurements of pulse rate, respiratory rate, blood pressure, oxygen saturations and temperature. The frequency of vital signs measurements is usually guided by the clinical condition of the patient.

Intermittent measurement of these vital signs can be time consuming for healthcare professionals,^2^ and therefore the desired frequency of observations is often not achieved.^3^ Infrequent measurement of vital signs may also miss clinical deteriorations between these measurements.^4^ Thus, more sustainable, accurate and less time-consuming monitoring methods would be highly desirable.

Wearable ambulatory monitors (AM) may provide an alternative to intermittent vital signs monitoring by enabling the continuous monitoring of vital signs parameters. In addition to reducing the burden of intermittent measurement of vital signs on staff, continuous monitoring has the potential to facilitate earlier detection of deranged physiological parameters.^5^ A major barrier to the clinical implementation of these wearable devices is their uncertain reliability, efficiency and data fidelity.^6^ In particular, the effect of motion on its accuracy is underinvestigated. Recent work by Louie *et al*
7 tested four non-ambulatory pulse oximeters and found that motion impaired performance throughout a clinically relevant range of measurements. Less accuracy was reported at lower arterial oxygen saturations (SaO_2_) which is undesirable in clinical practice.^7^

This study is part of the Virtual High Dependency Unit (vHDU) project, a collaboration between the Institute of Biomedical Engineering and clinicians from the Nuffield Department of Clinical Neurosciences at the University of Oxford. This is a phased project aiming to refine and integrate ambulatory monitoring systems for use in clinical practice. Previous phases have tested device wearability and in situ testing on hospital wards. The purpose of this study is to test the performance of selected devices in a simulated clinical setting which will involve participant movement and inducing low peripheral oxygen saturations.

## Methods

This protocol follows the Standard Protocol Items: Recommendations for Interventional Trials reporting guidelines.^8^

### Study objectives

Primary objective: To determine the specificity and sensitivity of currently available ambulatory vital signs monitoring equipment for the detection of hypoxia.

Secondary objective: To determine the effect of movement on data acquisition by currently available ambulatory vital signs monitoring equipment.

These objectives will be assessed by comparing continuous peripheral oxygen saturations, pulse rate, heart rate and respiratory rate data from each AM with arterial blood oxygen saturation measured through arterial blood sampling, pulse rate derived from the arterial blood signal, heart rate derived from standard care 3-lead ECG, and respiratory rate derived from capnography and manual counting.

### Study design

Prospective, observational cross-sectional cohort study. Vital signs parameters from study devices will be compared with ‘gold standard’ and ‘clinical standard’ measurements.

### Sample size

Our sample size calculation is based on the ISO 80601-2-61:2019 guideline for pulse-oximetry equipment accuracy testing. This requires at least 200 data points balanced across each decadal range (70%–80%, 80%–90%, 90%–100%) of the SaO_2_ range 70%–100%, from at least 10 subjects. Approximately 30 full data sets will be required, to yield sufficient data points for the primary and secondary outcomes; therefore, up to 45 healthy adult subjects who meet the inclusion criteria will participate in the study. For the broadest application to the largest group of participants, the subjects should vary in their physical characteristics to the greatest extent possible.

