**Figure 2 F2:**
[figure not shown]
Hypoxia study day set-up. Legend: 1: tablets linked with AMD devices (4 Samsung TAB A, each linked with one AMD: AP-20, WristOX2 3150 BLE, CheckMe^™^ O2 and VitalPatch^®^. 1 iPad four connected to the wavelet). 2: resuscitation trolley and oxygen. 3%–7% oxygen in nitrogen cylinder. 4: hypoxicator apparatus. 5: Philips monitor (model MX450) connected to laptop (IX trend software). 6: drip stand with the arterial line pressure bag.

During the hypoxia exposure phase, oxygen saturations from the ‘clinical standard’ Philips monitor will guide the titration of the hypoxicator. Seven per cent oxygen in nitrogen will be used to further lower FiO_2_ if required. An ABG will be sampled when the participant reaches and remains stable at each pre-specified target peripheral oxygen saturation level (95%, 90%, 87%, 85%, 83%, 80%). We specified these saturations to allow assessment for our use case of prompt detection of hypoxia in normal adult patients in a ward environment, including multiple assessments within the 83%–95% range, and one assessment at the top end of the 70%–80% range, considered severe hypoxia.

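### The sample size relies on balanced coverage of 70–100% SaO2, which the six planned saturation targets do not give at any number of participants

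*Protocol article*

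**What the plan says.** The Sample size section takes its basis from the ISO standard for pulse-oximeter accuracy testing. It reports the requirement as follows: "This requires at least 200 data points balanced across each decadal range", the decades being 70–80%, 80–90% and 90–100% SaO2, "from at least 10 subjects". It then concludes: "Approximately 30 full data sets will be required, to yield sufficient data points for the primary and secondary outcomes". Recruitment is set at up to 45.

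The hypoxia schedule is in Stage 2: hypoxia exposure phase. One arterial blood gas (ABG) is drawn once the participant is stable at each "target peripheral oxygen saturation level (95%, 90%, 87%, 85%, 83%, 80" (per cent). Titration follows the bedside monitor's SpO2. The same section explains the levels by the ward use case. It describes several assessments between 83% and 95% "and one assessment at the top end of the" 70–80% decade. The Abstract also gives 80% as the lowest level.

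The Collected data section adds a normoxia sample. The Analysis section follows the same standard in reporting the root-mean-square accuracy, A_rms. The primary outcome (Outcome analysis) is sensitivity and specificity at each level at or below 90%.

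**The concern.** The only stated basis for the sample size has two parts: a total of 200 points, and balance over three decades of SaO2. Sufficiency is asserted without separating the two. The schedule places almost all points at or above 80%, so the balance is a property that the section invokes and the design does not have.

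Two things are at stake:

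- An A_rms reported under this standard, next to a paragraph that cites balanced 70–100% coverage, could be read as an accuracy figure for that whole range. It would in fact describe roughly 80–100%.
- The paragraph carries the same count over to the primary outcome. A count of points chosen for an accuracy statistic does not say how precisely sensitivity and specificity are estimated at each level. The lowest level has by far the fewest positives.

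**Working it through.** **Inputs (all from the protocol article).** At least 200 points over three decades; about 30 data sets; maximum 45 participants (Sample size). Six targets, one ABG each: 95, 90, 87, 85, 83, 80% (Stage 2). One normoxia point (Collected data). Six movement-phase ABGs, taken before hypoxia is induced (Stage 1). At most 15 ABGs per participant (Blood sampling). No alpha, power, SD or precision target is given, so the calculation is a count.

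**1. Reproducing the figure of about 30.** Participants needed = 200 / points per participant, rounded up.

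- Normoxia plus six targets: 200/7 = 28.6, so 29. This matches about 30, and 30 × 7 = 210.
- Six targets only: 200/6 = 33.3, so 34.
- All 13 scheduled ABGs (1 + 6 + 6): 200/13 = 15.4, so 16.

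The stated figure therefore reproduces the total, using seven points per participant.

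**2. Nominal points per decade.** The results for each way of treating the boundary values are:

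| Counting rule | N = 30: 70–80 / 80–90 / 90–100 | N = 45 |
|---|---|---|
| Six targets; 80 low, 90 middle | 30 / 120 / 30 | 45 / 180 / 45 |
| Six targets; 80 low, 90 high | 30 / 90 / 60 | 45 / 135 / 90 |
| Six targets; 80 and 90 both middle | 0 / 150 / 30 | 0 / 225 / 45 |
| 80 low, 90 high, plus normoxia | 30 / 90 / 90 | 45 / 135 / 135 |
| As above, plus movement ABGs | 30 / 90 / 270 | 45 / 135 / 405 |

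The fourth row is the most favourable one that reaches 200 at N = 30. It is 1:3:3. The lowest decade holds 1/7 = 14.3% of the points (1/6 = 16.7% without normoxia) whatever the enrolment.

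**3. Against the requirement.** Equal thirds (assumed, since no tolerance is stated) need 200/3 = 66.7, about 67 points per decade. A looser 25% share needs 50. Both exceed the 45 available at full recruitment. A 20% share (40 points) would be reached as a count at N = 45, but the lowest decade would still be only 14–17% of the points collected.

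**4. Points actually below 80% SaO2.** The decades are defined on SaO2, while titration follows the monitor's SpO2. Assume SaO2 = target − over-reading + normal scatter with SD 1 to 3 points. Expected points below 80%, summed over the six targets:

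| Assumed monitor over-reading | N = 30 | N = 45 |
|---|---|---|
| −2 points | 1–9 | 1–14 |
| 0 | 15–22 | 23–32 |
| +2 points | 34–40 | 51–60 |
| +4 points | 60–63 | 90–94 |

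Only an over-reading of about 4 points brings the lowest decade to about a third of the target points. The protocol does not plan on any such bias.

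**5. Primary outcome, nominal counts at N = 30.** Positives are the targets at or below the level × 30. Negatives are 210 minus positives.

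| Level | Positives | Negatives |
|---|---|---|
| ≤90% | 5 × 30 = 150 | 60 |
| ≤87% | 4 × 30 = 120 | 90 |
| ≤85% | 3 × 30 = 90 | 120 |
| ≤83% | 2 × 30 = 60 | 150 |
| ≤80% | 1 × 30 = 30 | 180 |

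As an illustration at ≤80%, 28 of 30 detected gives an exact 95% interval of 78% to 99%. If only 15 samples were truly positive (no monitor bias, SD 1), 14 of 15 gives 68% to 99.8%.

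**The case against.** The strongest defence is that nothing is hidden. The Abstract says saturation goes down to 80%. Stage 2 states that only one assessment touches the lowest decade and gives the ward use case as the reason. The Analysis section follows the standard in how A_rms is calculated and does not itself claim 70–100% coverage. This justifies the choice of levels and makes it less likely that a careful reader is misled. It does not amend the Sample size section, which still cites the balance without qualification.

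Extra data do not rescue the balance. Movement ABGs precede hypoxia and so fall in the top decade. The 5–30 s sampling windows add readings at the same plateaus. Two ABGs remain under the cap of 15 if 13 are drawn. Spent at the 80% target they would raise the nominal count there to 1 + 2 = 3 per participant, but no section plans that.

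Several stronger readings are tempting, and the documents do not support them:

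- **That the total falls short of 200.** The 30 × 6 = 180 count leaves out the normoxia sample, which is planned. With it the total is 210.
- **That too few participants are recruited.** The mix is set by the target list, so enrolment has no bearing on balance.
- **That about half of the 80% samples will lie above 80% SaO2.** This needs an unbiased bedside monitor, which no section states. The plausible count below 80% is wide.
- **That the primary outcome as a whole lacks data.** Only the lowest level is thin; the higher levels have 60 to 150 nominal positives. The clinical standard is also used as a reference, and on it the 80% plateau lies near 80% by construction.

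Detailed tables of A_rms by decade and interval widths may sit in a full protocol or analysis plan. Their absence from the article is not the defect.

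**Conclusion.** The point holds as a contradiction between the Sample size section and the hypoxia schedule. The standard's total is met (210 at 30 participants). Its decade balance is not: at best the nominal split is 1:3:3, with 30 points in the lowest decade at N = 30 and 45 at N = 45, all at that decade's upper boundary. No enrolment changes this share.

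The nominal split rests only on the documents' figures. The 67-point benchmark assumes equal thirds, although a 25% share is also missed. The number of points truly below 80% SaO2 depends on the unknown bias of the bedside monitor: at N = 30, 15–22 with no bias and 34–40 with a 2-point over-reading, for assumed SDs of 1 to 3.

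For the primary outcome, the statement of sufficiency is unsupported as written, because it is not tied to counts or precision at any level. That is weaker than saying the data are insufficient.

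**What to change.** Reconcile the Sample size section with Stage 2 by rewording:

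1. State that the design meets the standard's total count but not its decade balance, and refer to Stage 2 for the reason.
2. Give the nominal points per decade (30/90/90 at 30 participants, 45/135/135 at 45) and say how the boundary values 80% and 90% are counted.
3. Limit the A_rms accuracy claim to the sampled range, about 80–100%.
4. Base the sufficiency statement for the primary outcome on the expected positives and negatives at each level and the precision they give, noting that ≤80% is the thinnest.

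No change to saturation targets, number of samples or enrolment is proposed. The cost is a few sentences and a narrower claim: accuracy can no longer be presented as covering 70–100%.

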### Recruitment

Up to 45 healthy volunteers will be recruited, with adverts placed in appropriate target locations such as college common spaces and university buildings. The adverts will contain a description of the study and the number and email contacts of one of the members of the research team.

Inclusion criteria for the study are: willing and able to give informed consent for participation in the study; men and women aged 18 or over; and in generally good health.

Exclusion criteria are: allergies to adhesive dressings (such as bio-occlusive dressings or micropore) or local anaesthetic (eg, lidocaine); intracardiac device (eg, permanent pacemaker) or previous wrist arterial line; epilepsy; angina, congenital heart disease or history of severe cardiopulmonary disease; history of anaemia (reported in the prescreening telephone call), haemoglobinopathy or haemoglobin below 100 g/L on first test; resting hypoxaemia (SpO2 <94%) or significant cardiopulmonary disease rendering exposure to alveolar hypoxia unsafe, as determined by the research physician; pregnancy or breast feeding; clotting disorders and use of antiplatelet or anticoagulant medication (such as aspirin); and claustrophobia precluding spell in the hypoxic exposure.

### Study procedures

#### Initial contact

Healthy volunteers will contact the research team via telephone/email to express their interest in the study. The research team will provide further information including the Participant Information Sheet (PIS). If volunteers wish to proceed, a telephone appointment will be arranged to complete a brief prescreening assessment with a research nurse/physiotherapist (supported by a senior anaesthetist).

#### Pre-screening assessment

During the prescreening telephone appointment, the study will be discussed further and general screening questions will be asked, to confirm eligibility. Questions will be encouraged to ensure the potential participant understands the study. If the potential participant agrees to take part, an appointment for the hypoxia exposure visit will be agreed.

### Study visit

#### Screening assessment

The screening assessment will be completed by an appropriately qualified, medically trained member of the research team, who will confirm eligibility for the hypoxic exposure phase. This will include a urinary pregnancy test for all female participants of childbearing potential. Pregnancy is an exclusion criteria for the study as the effects of hypoxia on pregnancy are unknown.^9^

#### Arterial line insertion

After confirmation of eligibility, an arterial line will be inserted into the non-dominant radial artery of each participant on the day of the study visit under local anaesthesia.

#### Initial blood gas sampling

The first arterial blood gas (ABG) measurement will be assessed by the anaesthetist to confirm haemoglobin concentration ≥100 g/L. If the haemoglobin is below this level, the participant will be withdrawn from the study, the arterial line removed and the participant advised to discuss this finding with their general practitioner (as stated in the PIS).

#### Placement of devices

Participants will wear several ambulatory monitoring devices (AMD) which may include a chest worn patch (VitalPatch^®^), a purely wrist worn device (Wavelet) and up to three wrist-worn devices with finger probe(CheckMe^™^ O2+, AP-20 and WristOX2 3150 BLE). The AMD detect various combinations of pulse oximetry, pulse rate, heart rate and respiratory rate (please refer to online supplementary appendix 1 for device details). Participants will be asked to wear a maximum of five study devices during the hypoxia exposure visit (figure 1).

10.1136/bmjopen-2019-034404.supp1Supplementary data

**Figure 1 F1:**
[figure not shown]
Devices placement example (dominant hand, combination 3).

#### Finger probe position randomisation

Up to three study device finger probes will be worn, in addition to the ‘clinical standard’ reference bedside monitor finger probe. The CheckMe^™^ O2+ will always be worn on the thumb as per manufacturer recommendation.^10^ To ensure parity of testing, the position of the other three finger probes on the second, third and fourth fingers will be randomised (using https://www.random.org/) per study visit day, ensuring an even distribution of placement, as per table 1).

**Table 1 T1:** Device combinations

Devices placement	Combination 1 (n=10)	Combination 2 (n=10)	Combination 3 (n=10)
Chest	VitalPatch^®^	VitalPatch^®^	VitalPatch^®^
Wrist	Wavelet	Wavelet	Wavelet
1st (thumb)	CheckMe^™^ O2+	CheckMe^™^ O2+	CheckMe^™^ O2+
2nd (index finger)	Philips monitor (MX450)	WristOX2 3150 BLE	AP-20
3rd (middle finger)	AP-20	Philips monitor (MX450)	WristOX2 3150 BLE
4th (ring finger)	WristOX2 3150 BLE	AP-20	Philips monitor (MX450)

#### Stage 1: movement phase

During the movement phase, participants will be seated in a chair and asked to complete a series of consecutive standardised movements, as detailed in table 2. An ABG and manual (counted) respiratory rate will be taken at the end of each movement.

**Table 2 T2:** Standardised movements to be tested

Movement	Task
Standing from chair using arms to push up/sit down	20x repetitions.
Tapping	Volunteer to tap a surface with all test side fingers simultaneously at the speed of a metronome set at 100 bpm for 2 min.
Rubbing	Volunteer to complete a sideways rubbing movement with all test side fingers simultaneously at the speed of a metronome set at 100 bpm for 2 min.
Drinking from plastic cup	20 x lift/drink/put down.
Turning page	50x page turns.
Using tablet	As per protocoled instructions (online supplementary file 2).

10.1136/bmjopen-2019-034404.supp2Supplementary data

#### Stage 2: hypoxia exposure phase

Participants will move to a bed and lie comfortably in a semi-recumbent, supine position (figure 2). A tight-fitting silicone face mask will be placed and connected to a hypoxicator unit (Everest Summit Hypoxic Generator, www.altitudecentre.com). If required, additional 7% oxygen in nitrogen from a cylinder will be entrained into the hypoxicator circuit to ensure tight control of fraction of inspired oxygen (FiO_2_) provided to the participant.^11^ Inhaled FiO_2_ will be monitored by an in-line gas analyser and end-tidal carbon dioxide (etCO_2_) will be also recorded via capnography using the Philips monitor MX450 (www.philips.co.uk).

**Figure 2 F2:**
[figure not shown]
Hypoxia study day set-up. Legend: 1: tablets linked with AMD devices (4 Samsung TAB A, each linked with one AMD: AP-20, WristOX2 3150 BLE, CheckMe^™^ O2 and VitalPatch^®^. 1 iPad four connected to the wavelet). 2: resuscitation trolley and oxygen. 3%–7% oxygen in nitrogen cylinder. 4: hypoxicator apparatus. 5: Philips monitor (model MX450) connected to laptop (IX trend software). 6: drip stand with the arterial line pressure bag.

During the hypoxia exposure phase, oxygen saturations from the ‘clinical standard’ Philips monitor will guide the titration of the hypoxicator. Seven per cent oxygen in nitrogen will be used to further lower FiO_2_ if required. An ABG will be sampled when the participant reaches and remains stable at each pre-specified target peripheral oxygen saturation level (95%, 90%, 87%, 85%, 83%, 80%). We specified these saturations to allow assessment for our use case of prompt detection of hypoxia in normal adult patients in a ward environment, including multiple assessments within the 83%–95% range, and one assessment at the top end of the 70%–80% range, considered severe hypoxia.

